### Data management {19}

A study-specific Data Management Plan (DMP) will be developed for the Co-CAT trial outlining in detail the procedures that will be put in place to ensure that high-quality data are produced for statistical analysis.

On completion of the trial and data cleaning, the study documentation will be transferred to a secure, GCP-compliant archiving facility. Participants’ identifiable information will be kept for 6 months unless participants give permission for their information to be kept in order to be contacted about research after the study has finished. This excludes any research documents with personal information, such as consent forms, which will be held securely at the University of Oxford for 3 years after the end of the study. Qualitative interview transcripts will be retained securely to support publications of findings from the study until they are no longer required. Prior to database lock, the Data Manager and the Trial Statistician will undertake a dataset review. Digitised consent/assent forms and an electronic record of consent/assent completed online will be stored for 3 years after the study is complete and then securely destroyed. The linkage information will be permanently destroyed at the end of the study. The only exception will be that if participants (parents) agree to be approached for future research, we will retain the consent form as the basis for retention of details and future approach. Those contact details will be held securely, separately from the research data, and will be kept updated. Audio-recordings will be stored until recordings have been transcribed verbatim, and transcriptions thoroughly checked. This means that audio files will be destroyed by the end of the study.

#### Source data

Source documents are where data are first recorded, and from which participants’ Case Report Form (CRF) data are obtained. These include, but are not limited to,Parent-reported questionnairesChild-reported questionnairesTherapist-reported questionnairesParent and therapist interviews

CRF entries will be considered source data if the CRF is the site of the original recording (e.g. there is no other written or electronic record of data). On all trial-specific documents, other than the signed consent, each participant will be referred to by the trial participant number/code, not by name.

#### Access to data

Direct access will be granted to authorised representatives from the Sponsor and host institution for monitoring and/or audit of the study to ensure compliance with regulations.

Access to personally identifiable data will be restricted on a need-to-know basis. This will include the PI, co-investigators, research staff involved in data collection, therapists, and clinical supervisors delivering the intervention.

Agreements will also be in place with external organisations (OSI hosting provider and software developer, a transcription service) who will be data processors and will require access to personal data collected in this study. Oxford University Third Party Security Assessments (TPSA) will be conducted for both organisations and they will be required to comply with the TPSA recommendation.

Anonymised trial data will be made available for open access on completion of the trial via the UK Data Service or another suitable repository. Qualitative interviews will not be shared in this way due to the difficulties in fully anonymising the data.

### Data recording and record keeping

All participants (parents, children, therapists) will be assigned a unique ID. A document that links the participant’s personally identifiable data with the participant ID will be stored separately from all other research data. Therapist records will refer to the study identifier of the parent from the participating family so that data can be linked. Sentry will be used to ensure that record of participant contact details (email, telephone number, address) is stored separately from other data. Sentry is an online secure data entry system developed in-house at PC-CTU and hosted at Oxford. It is designed to collect sensitive data, such as participant contact details, and securely retain them separate from a trial’s clinical data. Sentry can also act as a central participant portal to manage online eligibility, eConsent and ePRO—acting as an intermediary between the participant and the clinical databases. Sentry is accessed via a secure HTTPS connection and all stored sensitive data is encrypted at rest to AES-256 standards.

The main trial data will be entered directly into the participants’ CRFs in an electronic format by the participant or trial team (using REDCap database via Sentry). The use of REDCap is compliant with Good Clinical Practice and guidelines such as 21 CFR Part 11 via differentiated user roles and privileges, password and user authentication security, SSL encryption, and de-identification of Protected Health Information. Data will be hosted on network servers/drives which are maintained by University of Oxford MSD’s and are backed up every 24 h to and firewalls and authentication are in place to block any inappropriate access.

While all main trial data will be directly entered into electronic Case Report Forms (eCRFs), paper versions will be provided if access to the online CRF is not possible. In this case, the original copy of the CRF will be returned to the study team and a copy will be held at the research site. All CRFs (electronic or paper) will be date stamped upon receipt. A full pre-entry review and electronic data validation for all data entered into the clinical database will be provided by study-specific programmed checks (see Data Management and Checks section below). All paper data will be locked in secure cabinets and only the researchers will have access to the files. A separate database will be used to securely store all identifiable patient information required to contact patients and permit follow-up. Access to this information will be strictly on a need-to-know basis and databases will be password protected on a secure server.

Routine sessional treatment data will be captured within OSI (for the OSI+therapist support arm only) and this will be available to the research team in pseudo-anonymised form via the OSI researcher portal. The pseudo-anonymised data will be regularly exported from OSI in CSV form and saved on the study-restricted access OneDrive for merging (by study ID) with the main trial data at the point of statistical analysis. The OSI online platform is based in the European Economic Area and is compliant with NHS digital’s requirements for data and security. As noted above, OSI will be subject to a University of Oxford TPSA and will be required to comply with recommendations.

Qualitative interviews will be audio recorded using an encrypted digital audio recorder. Recordings will be held temporarily on these audio-recording devices for no more than 24 h before being securely transferred to a restricted access folder on the University of Oxford IT Network where they will be stored separately from all other research data in a restricted access OneDrive folder. The audio recording will be either (i) transcribed by a member of the research team (manually or using Teams) or (ii) sent securely via OneDrive to a transcriber with a contract with the university (and who has been subject to and found to comply with recommendations from a TPSA). The transcriber will be required to delete all audio files after returning the verbatim transcription to the research team.

Where Teams is used to transcribe interviews, the audio recording will be used to create a Teams transcript which will be automatically generated by Microsoft Teams in Nexus 365 STREAM, manually downloaded as a .vtt file to a temporary folder in the researcher’s computer, uploaded to Microsoft STREAM VTT cleaner to remove all coding from the transcript, and the bare text of the transcript then copied and pasted into a word document. The transcript will then be formatted, checked against the original audio, and names removed and saved to a secure restricted access OneDrive folder. The recording on MS STREAM and .vtt file will then be deleted. Transcripts will be de-identified.

### Data management and checks

The data management will be run in accordance with the University of Oxford Primary Care-Clinical Trials Unit (OC-CTU) Standard Operating Procedures, which are fully compliant with Good Clinical Practice (GCP). A PC-CTU data manager will be assigned to the study, as delegated by the CI, and will be responsible for overseeing the receiving, entering, cleaning, querying, analysing, and storing of all data that accrues from the study by designated persons.

#### Data entry

The data capture method used is Electronic Data Capture; therefore, single-pass entry is used rather than double-data entry. This is in accordance with the SOP PC-CTU_SOP_DM106_Data Entry.

#### Dataset reviews

· Full dataset reviews are conducted on a bi-monthly basis.· AE/SAEs will be entered by the trial team by single data entry (a 100% SDV will be conducted to ensure accuracy at the end of the trial).

Date of birth check:· The date of birth is entered by parents within the demographics questionnaire.· These will be checked periodically (twice a week) to ensure the child meets the age criteria (child should be aged 5–12 years at intake)

Data quality rules (AE/SAE Forms):· Looking at inconsistent data within the database· Data quality rules are run once a month. These include (reverse checks):The date the form was completed is prior to the start date of the adverse event.The date the form was completed is in the future.The date the PI was made aware of the event is prior to the start date of the adverse event.The date the PI was made aware of the event is in the future.The date the adverse event was resolved is prior to the start date of the adverse event.The date the adverse event was resolved is in the future.It has been recorded that the participant outcome was death; however, it has also been recorded that the action taken was ‘Continued with study’.The date provided is in the future.

Listing checks:· Report to ensure data is consistent across related forms.· These are run once a month by the data manager

Edit Checks:· There are 276 automatic edit checks that are built into the CDMS that fire upon submission of data.

Database rules and limits have been created to promote cleaner data follow entry. This means that variables can only accommodate certain values within a range to limit data entry mistakes. Limiting the free text box options and promoting the use of radio buttons and drop-down menus within the database results in cleaner data throughout.

#### Data storage and security

CDMS Back-up: Data stored on REDCap will be backed up on a nightly basis to the host server for 62 days. Back-up of the server file occurs nightly to two separate off-site storage facilities using University incremental back-up servers (IBIS). Each back-up is stored for approximately 6 months with one back-up retained for the 3 months preceding the start date of the retained daily back-ups.

Further details can be found in the Data Management Plan (available on request).

### Confidentiality {27}

The study will comply with the General Data Protection Regulation (GDPR) and Data Protection Act 2018, which require data to be de-identified as soon as it is practical to do so. The processing of the personal data of participants will be minimised by making use of a unique participant study number only on all study documents and any electronic database(s), with the exception of the CRF, where participant initials may be added. All documents will be stored securely and only accessible by study staff and authorised personnel. The study staff will safeguard the privacy of participants’ personal data.

Procedures will be compliant with:Data Protection Checklist https://researchsupport.admin.ox.ac.uk/policy/data/checklistPractical Considerations https://researchsupport.admin.ox.ac.uk/policy/data/practical

### Plans for collection, laboratory evaluation, and storage of biological specimens for genetic or molecular analysis in this trial/future use {33}

See above (26b) there will be no biological specimens collected.

## Statistical methods

### Statistical methods for primary and secondary outcomes {20a}

The statistical aspects of the study are summarised here. Details will be fully described in a statistical analysis plan (SAP). The SAP will be prepared by an independent statistician and finalised before any analysis takes place.

#### Description of the statistical methods

In accordance with CONSORT guidelines, we will record and report participant flow. Descriptive statistics of recruitment, drop-out, and completeness of interventions will be provided. Baseline variables will be presented by randomised group using frequencies (with percentages) for binary and categorical variables and means (and standard deviations) or medians (with lower and upper quartiles) for continuous variables. There will be no tests of statistical significance nor confidence intervals for differences between groups on any baseline variables.

##### Analysis of clinical outcomes

Analysis of the primary outcome will be performed using a generalised linear mixed effects model adjusting for stratification variables, and any baseline variables that are deemed to be highly prognostic of the outcome will be used to determine the treatment effect and 95% confidence interval. The mixed effect models will include the outcome as the response variable, time point, randomised group, and baseline score as fixed effects and a participant-specific random intercept. An interaction between time and randomised group will be fitted as a fixed effect to allow estimation of treatment effect at all time points. Non-inferiority is claimed if the lower limit of the 95% confidence interval around the standardised effect size is −0.33. A *P*-value for non-inferiority will also be calculated. A similar approach will be used for the other secondary outcomes.

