### Sample size {14}

Between 418 and 560 children (209–280 per group) with a primary anxiety problem and their parents will be randomised across the two treatment arms. This sample size is considered to be sufficient to provide a standardised noninferiority margin = 0.33 and between 80 and 90% power (allowing for 30% attrition). The required sample size was calculated using PASS 2019.

A sub-sample of up to 20–40 parents and therapists/supervisors from both arms will be involved in qualitative interviews to explore their experiences of treatment. We will purposively sample from parents who have reached 14 weeks post-randomisation until we reach saturation in terms of (i) representation across the sample for geographic, economic, and educational backgrounds and (ii) until no new themes are identified. We will also aim to recruit therapists who reflect differing characteristics (e.g. service provider type and location, demographic factors, and clinical backgrounds), as well as therapists’ supervisors. We have previously found that this number of participants is typically sufficient for data saturation.

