### Recruitment {15}

Participating families will be identified by their clinical teams. Clinical teams will follow their usual procedures to identify the child’s primary presenting problem. The clinical team will conduct an initial assessment of eligibility according to the inclusion and exclusion criteria. Where the clinical team identifies that the study inclusion criteria are met (and exclusion criteria are not), they will briefly outline the study to the parents. If parents express an interest in the study, they will be asked to provide an email address to which they will be sent a secured link to the study IT system where the parent will be able to access online information sheets which will provide further information about the study and what would be expected of the participants, alongside contact details for the study team (email and phone number) so that they can be contacted to answer any questions. There will also be video information (information sheet text being read aloud verbatim). In addition, there is dedicated, age-appropriate, online information including a video (consisting of the information sheet with text being read aloud verbatim) for the child. The parent will then be invited to provide online consent for themselves and their child. Where parents provide consent, a further email will be sent with a link for the child to provide assent.

Therapists whose role includes delivery of psychological interventions to children with anxiety problems within participating clinical teams will be invited to take part and consenting families will be allocated to these therapists for treatment. Allocation of families to therapists will be managed within participating clinical teams.

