## Assignment of interventions: allocation

### Sequence generation {16a}

Participants will be randomised in a 1:1 ratio to (i) OSI+therapist support or (ii) CAMHS treatment as usual for child anxiety problems within the COVID-19 context (C-TAU).

Minimisation by child age (≤8; ≥9), gender, service type (school based or not school based), and baseline anxiety-associated interference including permuted block size will be used to ensure balance across groups.

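### The primary model names only a participant random intercept although families share sites and therapists, so the interval that decides non-inferiority may be mis-sized in a direction the protocol does not settle

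*Protocol article*

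**What the plan says.** Under Analysis of clinical outcomes, the protocol article gives the structure of the primary model: "time point, randomised group, and baseline score as fixed effects and a participant-specific random intercept", plus a time-by-group interaction and adjustment for the stratification variables and for strongly prognostic baseline variables. Non-inferiority is read from the lower limit of the resulting 95% confidence interval.

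Trial design {8} describes a multi-site trial. Under Recruitment {15}, "consenting families will be allocated to these therapists for treatment", and each team decides which therapist sees which family. Under Sequence generation {16a}, the minimisation factors are child age, gender, baseline interference from anxiety, and "service type (school based or not school based". That last factor has two categories and is not site. Therapist does not appear.

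Sample size {14} states: "Between 418 and 560 children (209–280 per group) with a primary anxiety problem and their parents will be randomised". The basis is a "standardised noninferiority margin = 0.33" and "between 80 and 90% power", "allowing for 30% attrition". No ICC or design effect is mentioned anywhere in the article.

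The linking data exist. Data recording and record keeping says: "Therapist records will refer to the study identifier of the parent from the participating family so that data can be linked".

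**The concern.** A participant random intercept handles the repeated measurements on one family. It does nothing for similarity between families treated by the same therapist or in the same service. Adjusting for the stratification variables does not help, because neither site nor therapist is one of them. The comparator is each service's own current practice, so the contrast between the arms could itself vary from service to service.

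The decision rests on one limit of one interval. If the standard error is too small, the chance of a false claim of non-inferiority exceeds the nominal 2.5%. If it is too large, precision is lost. The planned numbers contain no slack for the first case.

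A related weakness lies in a secondary comparison. Therapists complete an experience questionnaire after finishing with each family (Participant timeline {13}; Treatment credibility and experience). Additional quantitative analyses plans to compare experience scores between arms as plain means. A therapist with several families supplies several ratings, and that comparison treats them as independent.

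**Working it through.** **Inputs from the protocol article:** standardised margin 0.33 (so SD = 1), power 80–90%, attrition 30%, 209–280 randomised per arm, 1:1 allocation, decision by a two-sided 95% interval (one-sided 0.025).

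**Assumptions, because the article gives no figure:** true difference 0; ICC 0.01–0.10; 2–5 analysed families per therapist, with 10 as an extreme.

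**Step 1: reproduce the stated sample size.** With independent observations, n per arm = 2(z₀.₉₇₅ + z_power)² / 0.33².
- 80% power: 145 by the normal approximation, 146 by the t-based calculation; 146/0.7 = 208.6, so 209. This matches.
- 90% power: 193 and 194; 194/0.7 = 277.1, so 278, within 1% of the stated 280.
- A one-sided 0.05 level gives 163–165 and 226, which does not match.

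The stated range is therefore an independent-observations calculation with no clustering allowance.

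**Step 2: therapists nested in arm.** With m families per therapist:
- design effect DE = 1 + (m − 1) × ICC
- true one-sided error of the unadjusted interval = Φ(−1.96/√DE)
- power of a correctly sized interval = Φ(0.33/√(2·DE/n) − 1.96), with n = 0.7 × 209 ≈ 146 or 0.7 × 280 = 196 analysed per arm

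With DE = 1 the power formula gives 80.5% and 90.4%.

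| m | ICC | DE | One-sided error | Power, 418 randomised | Power, 560 randomised |
|---|---|---|---|---|---|
| 2 | 0.01 | 1.01 | 2.6% | 80.1% | 90.2% |
| 2 | 0.05 | 1.05 | 2.8% | 78.6% | 89.0% |
| 3 | 0.05 | 1.10 | 3.1% | 76.7% | 87.6% |
| 5 | 0.02 | 1.08 | 3.0% | 77.4% | 88.2% |
| 5 | 0.05 | 1.20 | 3.7% | 73.0% | 84.7% |
| 5 | 0.10 | 1.40 | 4.9% | 66.4% | 78.8% |
| 10 | 0.10 | 1.90 | 7.8% | 53.4% | 65.9% |

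The last two rows lie outside the range used for the conclusion and show only where the extremes lead.

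**Step 3: a cluster effect crossed with arm.** This covers a common site effect, since individuals are randomised and nothing suggests that a site delivers one arm only. It also covers therapists who treat both arms equally. If the effect is left out, the unadjusted standard error divided by the correct one is about 1/√(1 − ICC).
- ICC 0.01: 1.005, so 0.5% too wide; one-sided error 2.4%.
- ICC 0.10: 1.054, so 5.4% too wide; one-sided error 1.9%.

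**Step 4: treatment effect varying by site or therapist.** Crossing does not remove this component. The unadjusted standard error is then too small for inference beyond the particular sites and therapists in the trial. The article gives nothing from which to size it, so no figure is offered.

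**The case against.** The strongest reply is that the article calls its statistical section a summary and leaves details to an analysis plan that is not shown. It lists what the model will include and does not say that nothing else may be added. That is fair, and the plan may contain these terms. But the article leaves the choice of prognostic baseline covariates open, whereas it writes down a random-effects structure. The point is about what is written.

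A reader might infer that the interval is probably too narrow, and that site and therapist clustering together raise the risk of a false non-inferiority claim. The documents do not support that. They give no ICC and no families per therapist, and they do not say whether a therapist treats one arm or both. The adverse-event section speaks of therapists working with families in either arm, which is compatible with crossing. A common site effect acts in the conservative direction.

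A reader might also infer that the trial is underpowered. That does not follow. At 560 randomised, power stays at 84.7–90.2% over ICC 0.01–0.05 and 2–5 families. Baseline adjustment may offset the loss: if the margin is scaled to the raw SD and the baseline–outcome correlation is 0.5 (both assumptions), the variance factor is 1 − 0.5² = 0.75, and 0.75 × 1.20 = 0.90. This can restore power, but it does not correct an interval that ignores remaining clustering.

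Two cautions about the remedy also stand. A plain therapist intercept does not capture therapists who differ in how well they deliver one arm relative to the other. And therapist is assigned after randomisation and may be undefined for families who never start treatment but are analysed as randomised.

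**Conclusion.** The written model omits two sources of clustering that the design creates, and the sample size makes no allowance for them. The deciding interval may therefore be mis-sized, but neither the direction nor the size can be fixed from the protocol.

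It is too narrow if therapists mainly treat one arm or if the effect varies by therapist or site. Under assumed nesting, with ICC 0.01–0.05 and 2–5 families per therapist, the one-sided error is 2.6–3.7%. It is slightly too wide for a common site effect or fully crossed therapists.

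With small therapist caseloads the consequence is minor. This is a specification worth improving, not a demonstrated error in the result. The treatment of repeated therapist ratings as independent is the clearer fault, but it affects only a secondary comparison.

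**What to change.** 1. Add a site random intercept to the primary model.
2. State whether therapists treat one arm or both. Prespecify a sensitivity analysis of the non-inferiority interval with a therapist random effect, nested or crossed as delivered, that allows the treatment effect to vary by therapist or by site.
3. In that analysis, give a rule for families with no therapist and a fallback if the model does not converge.
4. Analyse the per-family therapist experience ratings with a therapist random effect or cluster-robust standard errors in place of plain mean comparisons.

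Therapist records are already linkable to families, so this needs no new data collection. The article gives 3 August 2022 as the end of recruitment, so the change concerns the model and not the sample size. It should be fixed before any analysis. The cost is a possibly slightly wider interval and a little more analysis work.

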### Outcomes {12}

#### Primary measures and objective

*Primary objective:* To evaluate the parent-reported clinical effectiveness of a brief parent-led cognitive behavioural treatment (CBT) delivered by the OSI platform with therapist support (OSI+therapist support) for the treatment of child anxiety compared to COVID-19 treatment as usual (C-TAU) in CAMHS throughout the next phases of the COVID-19 pandemic.

*Primary outcome measure*: The Child Anxiety Impact Scale-parent report (CAIS-P) captures the degree to which anxiety is interfering in the child and family’s life, measured at 26 weeks post-randomisation.

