### Participant timeline {13}

Where parents and their children provide online consent or assent, respectively, they will be asked to complete online baseline assessments (all questionnaires), prior to randomisation. After randomisation, parents will be asked to complete a further short questionnaire about treatment expectations and acceptability. Treatment in both arms will be organised by the clinical teams who will be requested to start as soon as possible and at most within 12 weeks of randomisation. Families allocated to the intervention arm will access OSI and a member of the clinical team will provide support as they work through each OSI module. Participating parents and children in both arms (OSI+therapist support and C-TAU) will be sent a link to complete post-treatment and follow-up assessments (questionnaires) online 14 and 26 weeks after randomisation.

Therapists will provide information on COVID-19 treatment as usual for each participant at the start of their treatment within the therapist treatment logs in order for us to be able to describe what services are delivered in the COVID-19 context, specifically the treatment approach being followed, who they are having contact with (e.g. child, parent, both), and for how long.

Therapists will provide brief demographic information at the study outset, will record information on activity with each participating family, and will complete a brief questionnaire about their experience of the treatment after completing treatment with each participating family.

We will also conduct qualitative interviews with a subgroup of parents and therapists/supervisors (*n*= 25–40), between 14 and 26 weeks after randomisation, purposively sampled on the basis of demographics, and we will continue to sample to ensure variability in treatment outcomes across both arms, if possible, to explore and to understand therapist and parents’ experiences of treating child anxiety in this context.

SPIRIT schedule of enrolment, interventions, and assessments

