#### Impact of child anxiety

The Child Anxiety Impact Scale- parent report (CAIS-P/C): The CAIS-P/C will be used to determine the extent to which anxiety interferes with the child’s life. This measure covers three psychosocial domains (academic, social activities, and home/family environments) and consists of 27 items rated on a 4-point scale. An additional 4 ‘global’ items assess overall interference. There are versions for children and parents to complete, both of which have been shown to have good psychometric properties [21, 22]. The CAIS-P/C will be completed at baseline and then at 14 and 26 weeks post-randomisation by both parent and child.

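### As stated, the primary model pools residual variance over 14 and 26 weeks, so the 26-week interval that decides non-inferiority has the right width only if the two variances are equal

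*Protocol article*

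**What the plan says.** Under Analysis of clinical outcomes, the protocol article commits to this: "Analysis of the primary outcome will be performed using a generalised linear mixed effects model adjusting for stratification variables". The listed terms are "time point, randomised group, and baseline score as fixed effects and a participant-specific random intercept". One interaction is named: "An interaction between time and randomised group will be fitted as a fixed effect to allow estimation of treatment effect at all time points". No visit-specific residual variance, unstructured covariance, robust standard error or baseline-by-time term is mentioned.

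The decision rule is "Non-inferiority is claimed if the lower limit of the 95% confidence interval around the standardised effect size is −0.33", which I read as the limit lying above −0.33. The primary outcome, the CAIS-P, "captures the degree to which anxiety is interfering in the child and family’s life, measured at 26 weeks post-randomisation". The model has two post-baseline visits: "The CAIS-P/C will be completed at baseline and then at 14 and 26 weeks post-randomisation by both parent and child".

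The opening of the Statistical methods section calls this a summary and leaves the details to an SAP, which is not at hand.

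**The concern.** A participant random intercept with one residual variance gives every visit the same total variance given baseline, namely the intercept variance plus the residual variance. Nothing in the protocol supports equality at 14 and 26 weeks, and the timetable gives reason to doubt it. Clinical teams are "requested to start as soon as possible and at most within 12 weeks of randomisation", and OSI has seven modules with weekly sessions. A family that starts at the limit is therefore about two weeks into treatment at the 14-week visit (14 − 12 = 2), while others may have finished. Treatment stage differs between the two visits, so residual spread may differ too.

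The non-inferiority claim depends on one limit of one interval at one visit. If that interval borrows variance from a less variable visit, it is too short and non-inferiority is declared too often. If it borrows from a more variable visit, the trial loses power it has paid for.

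Missing data add a secondary reason. The design allows for 30% attrition, and section {20c} relies on the mixed model for data missing at random. That reliance is safer when the covariance is not constrained.

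**Working it through.** **Reproducing the plan's own figure.** Sample size {14} states a "standardised noninferiority margin = 0.33 and between 80 and 90% power (allowing for 30% attrition"), with 209 to 280 per group. In SD units with one-sided 2.5% error:

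- 80% power: n = 2(1.960 + 0.842)²/0.33² → 145 per group; 145/0.7 → 208. The t-based version gives 146, and 146/0.7 → 209.
- 90% power: n = 2(1.960 + 1.282)²/0.33² → 193 per group; 193/0.7 → 276. The t-based version gives 194, and 194/0.7 → 278.

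The stated 209 and 280 are reproduced closely. The sample size is not in dispute, and the check confirms 2.5% one-sided as the nominal error.

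**Inputs for the interval.** The model structure, the decision rule and the 26-week time point come from the protocol. The ratio k = (residual SD at 26 weeks)/(residual SD at 14 weeks), both given baseline, is an assumption, because the protocol reports no SD or correlation by visit.

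**Closed form, complete data, n per arm.**

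- True variance of the 26-week contrast: 2σ₂₆²/n.
- Variance the model reports: 2·[(σ₁₄² + σ₂₆²)/2]/n.
- Ratio of reported to true standard error: r = √[(1 + k²)/(2k²)]. The sample size cancels.
- One-sided error at the margin: P(Z > 1.96 r).

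Example, k = 1.2: (1 + 1.44)/(2 × 1.44) = 2.44/2.88 = 0.847; r = 0.920; 1.96 × 0.920 = 1.80; error 3.56%.

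| k | r | one-sided error | 95% CI coverage |
|---|---|---|---|
| 0.8 | 1.132 | 1.33% | 97.35% |
| 0.9 | 1.057 | 1.91% | 96.17% |
| 1.0 | 1.000 | 2.50% | 95.00% |
| 1.1 | 0.956 | 3.05% | 93.89% |
| 1.2 | 0.920 | 3.56% | 92.88% |
| 1.3 | 0.892 | 4.02% | 91.96% |

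**Simulation of the stated model by REML.** Settings: 280 per arm, between-visit residual correlation 0.6, 20% missing at 14 weeks and 30% at 26 weeks (completely at random), 4,000 runs.

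- k = 1.2: r = 0.920, coverage 92.9%, error 3.6%.
- k = 1.0: r = 0.998, coverage 94.6%, error 2.5%.
- k = 0.83: r = 1.105, coverage 97.0%, error 1.5%.

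The closed form therefore holds up with missing data of this kind.

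**The shared baseline slope, taken alone.** With k = 1 and true slopes of 0.7 then 0.4, or 0.4 then 0.7, r is 0.996 and 0.999 and coverage is 95.0% and 94.9%. With k = 1.2, adding baseline-by-time (2,000 runs) leaves coverage at 92.3% with complete data and 91.7% with missing data. The variance assumption drives the problem, not the slope.

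**Converting from raw SDs.** k is the ratio after adjusting for baseline, so k = (raw SD ratio) × √(1 − r₂₆²)/√(1 − r₁₄²), where r₁₄ and r₂₆ are the correlations with baseline. Suppose these are 0.65 at 14 weeks and 0.45 at 26 weeks. Equal raw SDs then give k = √0.7975/√0.5775 = 1.175 and an error of 3.4%. Swapping the two correlations gives k = 0.85 and 1.6%. Both correlations are illustrative assumptions.

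**The case against.** The strongest reply is that covariance structure and type of standard error are SAP detail, and the SAP is not shown. A random intercept can be combined with visit-specific residual variances or robust standard errors, and the protocol excludes neither. This stands in part: the article does not compel a pooled variance. But it goes beyond silence, since it names the random effect and the full list of fixed terms, and the usual reading of that list pools the variances.

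A reader might infer from the late treatment starts that 26-week scores must be the more variable, and so that the interval is too narrow. The documents do not support that step. Twelve weeks is an upper limit, and the protocol labels the 14-week visit post-treatment. A 14-week sample mixing barely treated, part-treated and finished children could be the more variable one, with treatment stage more uniform by week 26. In that case the test is conservative.

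A reader might also blame the single baseline slope for a narrow interval. That slope comes from having no baseline-by-time term, not from the random intercept, and the simulation shows no material narrowing from it.

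**Conclusion.** The point holds in conditional form. Read in the usual way, the stated model makes the deciding 26-week interval depend on equal residual variances at the two visits. If the 26-week residual SD is 10% to 30% larger, one-sided error rises from 2.5% to about 3.1% to 4.0%. If it is 10% to 20% smaller, error falls to about 1.9% to 1.3% and precision is wasted. These figures rest on a single common residual variance and on assumed values of k. The protocol fixes neither the size of k nor its direction, so it does not show that the trial's error rate is inflated. The case for changing the model is that the alternative is right in either direction and costs almost nothing.

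**What to change.** Keep the repeated-measures model and its fixed effects. Replace the random intercept and single residual variance with an unstructured within-participant residual covariance over 14 and 26 weeks, so that each visit has its own variance. State that the primary contrast and its 95% confidence interval are the 26-week group difference from that model. Do the same for the secondary outcomes measured at both visits. A baseline-by-time term may be added for efficiency, but it is not a substitute.

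Cost: one sentence in the SAP and one extra variance parameter (three covariance parameters instead of two), or two extra parameters with baseline-by-time. No new data are needed. If the SAP already specifies visit-specific variances, only the protocol's description needs to be brought into line.
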